**Methods/Design:**

This is a randomized, 1:1, double-blind, placebo-controlled clinical trial.

The study takes place at two centers in Chile: University of Chile Clinical Hospital and San Borja Arriarán Clinical Hospital.

The subjects will be 134 adults with acute myocardial infarction with indication for percutaneous coronary angioplasty.

This intervention is being performed as a pilot study, involving high-dose vitamin C infusion plus oral administration of vitamin E (Vitamin-treatment group) or placebo (Control group) during the angioplasty procedure. Afterward, the Vitamin-treatment group receives oral doses of vitamins C and E, and the Control group receives placebo for 84 days after coronary angioplasty.

Primary outcome is infarct size, assessed by cardiac magnetic resonance (CMR), measured 6 and 84 days after coronary angioplasty.

Secondary outcomes are ejection fraction, measured 6 and 84 days after coronary angioplasty with CMR, and biomarkers for oxidative stress, antioxidant status, heart damage, and inflammation, which will be measured at baseline, at the onset of reperfusion, 6 to 8 hours after revascularization, and at hospital discharge.

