**Inclusion criteria**	
1	Subjects may be of either sex and must be at least 18 years old
2	Subjects must have indication of primary percutaneous coronary angioplasty (PCA):
	-Angina or equivalent at least 120 minutes in duration
	- Electrocardiogram with ST-segment elevation myocardial infarction that concerns more than two contiguous leads (>2 mm)
3	Presentation within 12 hours of symptoms onset
4	First myocardial infarction
5	Primary PCA must show a pre-PCA TIMI flow of 0
6	Subject must be able and willing to sign informed consent

**Table 2 T2:** Exclusion criteria of the study protocol

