### Sample size

Taking into account that until 50% infarct size is due to reperfusion damage, a minimal efficacy of the intervention is considered to reach a relative improvement up to 25% infarct size. Similar studies applying the same method have provided the accuracy of measurements as variance value. The sample size was calculated from the following formula [76]:

$$n=2{\left(\mathrm{ZS}+\mathrm{ZP}\right)}^{2}x\;S^{2}/{\left(\mathrm{MA}–\mathrm{MB}\right)}^{2}$$

Where *n* is the sample size for each group, “ZS” corresponds to the level of significance (5%), “ZP” represents the potency (80%), “MA” is the mean of supplemented group,MB, the mean of the placebo group (control), and S is the variance of CMR determination for assessment for IS. A 10% patient loss was considered for the purposes of this calculation. This calculation rendered a sample size of 66 patients for each branch (placebo and supplemented). This sample size is suitable to be covered by the population of patients being treated for PCA in the Cardiovascular Department, University of Chile Clinical Hospital, and Cardiovascular Center, San Borja Arriarán Clinical Hospital, during the estimated period (3 years).

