### Randomization and followup

Patients will be randomly allocated to one of the two groups. The allocation sequence will be centrally generated, stored, and assigned by using online randomization software (http://www.randomization.com) in random permuted blocks, each consisting of a box containing six treatment kits allocated in a placebo-to-vitamin treatment, 1:1 ratio for each participating center.

Random allocation is generated by intervention of the technician responsible for the treatment assignment to recruited patients, according to the sequence already established through the randomization method indicated previously. The reasons for losses and exclusions after randomization will be provided.

Neither participants, nor care providers, nor the investigators are aware of the treatment assignments. Adverse events, unintended effects and technical problems will be recorded.

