### Statistical analyses

Results of continuous variables will be expressed as mean ± standard deviation (SD). Comparison between parametric variables will be performed by using Student *t* test for unpaired samples. Nonparametric variables will be expressed as median (interquartile range) and compared through Wilcoxonrank-sum test. The significant differences for normally distributed variables will be compared with Student *t* test analysis of variance (ANOVA) for repeated measures. The significant differences for non-normally distributed variables will be compared by using the Mann–Whitney *U* test. Categoric variables will be expressed as numbers and frequencies (percentage). The Fisher Exact test with Katz approximation will be used to compare adverse-event frequencies.

Determination and data obtained for infarct size and ventricular function by cardiac resonance will be evaluated by two independent individuals with the purpose of applying the concordance kappa index. Among the limitations of using infarct size as an outcome, is that the use of final infarct size carries the risk of imbalances in baseline myocardium at risk, according to treatment group, as well as comparing different AMI locations, which may have different sensitivity to the therapy [80].

In addition to this, the groups may have variable time to reperfusion and other confounding variables that determine infarct size [81,82]. Whereas some of these difficulties may have been corrected through a careful stratification on entering the study, this option was discarded, given the small sample size of this study. We are currently considering an analysis of the data though a linear regression model, adjusted by all confounding variables, such as those mentioned before, and others present in the current literature [83]. *P*< 0.05 will be considered statistically significant. Results will be analyzed by using Stata version 8.0, Microsoft Excel,and Graphpad Prism 4.0.

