## Trial status

The PREVEC trial began recruitment in February 2013. Forty-three patients have been enrolled to date (3 June 2014) The trial is scheduled to end in March 2016.

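### Infarct location is named as a threat to the primary outcome, yet stratification is set aside because the trial is small and only unadjusted comparisons are fixed; location and centre should be committed covariates

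*Protocol article*

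**What the plan says.** Under Statistical analyses, the protocol article gives several limits of infarct size as an outcome: unequal myocardium at risk between groups, "comparing different AMI locations, which may have different sensitivity to the therapy", variable time to reperfusion, and other confounders. It allows that stratification at entry could have dealt with some of these, and continues: "this option was discarded, given the small sample size of this study".

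The same section fixes an unpaired Student t test, or a rank test for non-normal data, and mentions a repeated-measures ANOVA. No covariate is attached to any of them. A linear regression adjusting for all the confounders is described only as something being considered.

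Under Randomization and followup, kits come in boxes of six, "allocated in a placebo-to-vitamin treatment, 1:1 ratio for each participating center". Allocation is therefore balanced by centre but by no prognostic factor.

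Two other places show that location is available. Table 1 requires, for entry, "Electrocardiogram with ST-segment elevation myocardial infarction that concerns more than two contiguous leads". The Interventions section says that location and extent of the infarct will be recorded. Under Trial status: "Forty-three patients have been enrolled to date".

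**The concern.** Small size is a sound objection to crossing many factors. It is not a sound objection to balancing or adjusting for one or two strong ones, because the expected chance gap between arms shrinks as the sample grows. The article names a threat and its remedy, declines the remedy on grounds of size, and leaves the analytic substitute undecided. As written, neither the allocation nor a committed analysis protects the primary comparison against an uneven split by infarct location.

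Two things are at stake. One is precision: variance that a recorded baseline factor could remove stays in the error term. The other is credibility: if the arms differ visibly on location, readers will ask whether the infarct-size difference reflects the vitamins or the mix of infarcts. Choosing the covariates after seeing that imbalance would then look data-driven.

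**Working it through.** **Inputs from the protocol article.** Sample size section: 66 per arm, 5% significance, 80% power, 10% loss. Randomization section: 1:1 in blocks of six within each of two centres. The group means and S have no numerical values, so 66 cannot be rebuilt forwards.

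**Back-solving the design effect.** 60 × 1.1 = 66 per arm (132 in all). 60 / 0.9 = 66.7, rounded up to 67 (134 in all), which matches the abstract: "The subjects will be 134 adults with acute myocardial infarction with indication for percutaneous coronary angioplasty". Both point to about 60 evaluable per arm. Taking the 5% as two-sided (the article does not say), the implied standardised difference is (1.960 + 0.842) × √(2/60) = 0.51 SD.

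**Assumptions not in the documents.** Location has two levels (anterior or other) with share p, and explains a fraction R² of infarct-size variance, taken as 10-30%.

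**Chance of a location gap of 10 points or more.** With SE = √(2p(1−p)/n), at n = 66 and p = 0.45: SE = √(0.495/66) = 0.0866, and 0.10/0.0866 = 1.155, so the two-sided probability is 24.8%. Exact enumeration gives 25.5%.

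| p | normal, 66 per arm | exact, 66 per arm |
|---|---|---|
| 0.2 | 15.1% | 15.6% |
| 0.3 | 21.0% | 21.7% |
| 0.4 | 24.1% | 24.8% |
| 0.5 | 25.1% | 25.8% |

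At 60 evaluable per arm and p = 0.4-0.5, the exact figure is about 31%.

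Simulating the planned blocks of six within centre (132 patients, two equal centres, 4,000 runs) gives 25.0% at p = 0.4 and 26.7% at p = 0.5. Centre blocking therefore does nothing for location.

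**Is small size the right reason?** At 400 per arm and p = 0.5, SE = √(0.5/400) = 0.0354 and the chance of a 10-point gap is about 0.5%. The problem comes from the small sample. In the same simulation, stratifying from the start by centre and location (four strata of about 33 patients, or 5 to 6 boxes each) gave no 10-point gap in 4,000 runs. Even 48 strata gave 9-11%, still below no location stratification.

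**What a gap does to the unadjusted estimate.** The location effect in SD units is √(R²/(p(1−p))). At R² = 0.20 and p = 0.45 this is √(0.20/0.2475) = 0.90. A 10-point gap moves the estimate by 0.10 × 0.90 = 0.09 SD (0.06 at R² = 0.10, 0.11 at R² = 0.30), in either direction.

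**What adjustment gains.** Adjusted power ≈ Φ(2.802/√(1−R²) − 1.960):

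- R² = 0 (unadjusted): Φ(0.842) = 80%
- R² = 0.10: Φ(2.953 − 1.960) = 84%
- R² = 0.20: Φ(3.133 − 1.960) = 88%
- R² = 0.30: Φ(3.349 − 1.960) = 92%

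**What stratifying from now on would gain.** 134 − 43 = 91 patients remained at the status date. Simulated with 43 unstratified and 91 stratified by location within centre, the chance of a 10-point gap falls to about 5-6%, or about 8-9% after 10% random loss.

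**The case against.** The option the article rejects is stratification across several factors, not one. Myocardium at risk, location, time to reperfusion and others, crossed with two centres in about 132 patients, would give sparse strata, and the Discussion says there is no imaging before angioplasty. This stands, and it limits the criticism of the rationale to one or two factors. Blocking within centre plus covariate adjustment is also an accepted design for a pilot trial, and the article does mention regression. But it mentions it only as a possibility, with an open-ended covariate list.

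Three stronger readings are tempting, and the documents do not support them.

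- A reader might infer that the planned test is biased or has an inflated error rate. It is not: chance imbalance under randomisation leaves the unconditional type I error intact.
- A reader might infer that an adverse gap takes power well below the planned 80%. The planned figure already averages over chance imbalances through the total SD, and a favourable gap is equally likely. A gap of 10 points or more in the harmful direction arises in about one trial in eight.
- A reader might infer that the allocation must be rebuilt. With 43 patients enrolled, that is a trade-off. Treatment starts about 30 minutes before angioplasty, while the TIMI flow criteria are settled at angiography, so later exclusions and missed scans would erode balance achieved at allocation. Once location is in the model, stratification adds little further precision.

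**Conclusion.** The point holds as a weakness in the stated rationale and in the primary analysis, not as an invalid design. At 66 per arm the chance of a 10-point or larger location gap is about 25% for a share of 40-50%, and about 16% for a share of 20%. The location share and the variance explained (10-30%) are assumptions, and the 0.51 SD effect is back-solved. On that basis, committing to adjustment lifts power from 80% to about 84-92% with data already planned. A main-effect term deals with imbalance and precision. It does not answer whether the effect differs by location, which the article also raises and which a trial of this size can only explore.

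**What to change.** In the Statistical analyses section, make the comparison of infarct size a pre-specified linear model with treatment, centre (the blocking factor) and infarct location (anterior or other), and keep the unadjusted test as a sensitivity analysis. Define location by a rule fixed before unblinding; the qualifying ECG allows this without a new test. Replace the sentence on sample size with an accurate reason, for example that crossing several factors would give sparse strata and that location is handled by adjustment.

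The cost is a short amendment and two degrees of freedom, with no new data.

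Optionally, stratify the remaining allocations by location within centre. This would need new lists and box labels for about 91 patients and two open boxes per centre. It could leave up to four incomplete blocks and carries a small risk of taking a kit from the wrong box. The gain over adjustment is mainly balance and credibility, so it need not be required.

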### Interventions

All patients will be asked to sign the informed consent before beginning the protocol. For those patients allocated to receive vitamin treatment, the intervention will be started as soon as the patient has signed the informed consent. The protocol will be started by administering an unique oral dose of vitamin E as α-tocopherol (800 IU) and an intravenous infusion of vitamin C as sodium ascorbate (320 m*M*) infused at a 10-ml/min flow rate during the initial hour and at 3 ml/min rate during the following 2 hours. Percutaneous coronary angioplasty will be performed about 30 minutes after initiating the vitamin C infusion. Oral doses of vitamin E (400 IU/day) and vitamin C (500 mg/12 hours) will be taken by the patients for 84 days after PCA.

For those patients allocated to receive placebo treatment, the 800-IU oral dose of vitamin E will be replaced for two vegetable oil capsules (400 mg each). The intravenous infusion of vitamin C will be replaced by an equal sodium chloride solution volume having the same osmolality as the vitamin C infusion administered to supplemented patients. The 400-IU oral doses of vitamin E will be replaced by vegetable oil (400 mg), and oral doses of vitamin C will be replaced with inert starch microgranules (500 mg). The pharmaceutical forms of vitamin C and E are indistinguishable from their respective placebos.

After the initial evaluation, patients will go to the catheterization laboratory. According to the standard protocol in AMI, an angiography will be performed to identify the infarct-related artery. The location and extent of AMI (number of arteries involved), percentage of stenosis, TIMI flow, type of stent, and so on, will be recorded. Immediately before coronary arteriography to confirm total occlusion of one coronary artery, a basal blood sample will be drawn from the antecubital vein. Three more blood samples will be obtained: immediately after successful reperfusion, at 6 to 8 hours after finishing the revascularization process and before hospital discharge.

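### The listed tests for infarct size are unadjusted, and the only adjusted model is undecided, with an open covariate list and no stated rank

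*Protocol article*

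**What the plan says.** All of this is in the protocol article.

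- **Tests.** Statistical analyses: "Comparison between parametric variables will be performed by using Student" *t* test for unpaired samples. Rank-sum or Mann–Whitney tests serve non-normal variables, and a repeated-measures ANOVA is also mentioned. No covariate appears in any of these. None is assigned to infarct size by name, but the unpaired *t* test is the natural reading for a normally distributed outcome and matches the two-mean formula under Sample size.
- **Randomisation.** Randomization and followup describes permuted blocks of six kits, "allocated in a placebo-to-vitamin treatment, 1:1 ratio for each participating center". No listed analysis uses centre.
- **Prognostic factors.** Statistical analyses warns of imbalance in myocardium at risk, of differing infarct locations and of variable time to reperfusion. It adds that stratification on entry was rejected because the sample is small.
- **Adjusted model.** "We are currently considering an analysis of the data though a linear regression model, adjusted by all confounding variables". The sentence goes on to take in further, unnamed variables from the literature. It does not say how this model ranks against the *t* test.
- **Data at hand.** Interventions: "The location and extent of AMI (number of arteries involved), percentage of stenosis, TIMI flow, type of stent, and so on, will be recorded". Table 1 requires presentation within 12 hours of symptom onset, so onset time has to be known at entry.
- **Status.** Trial status reports 43 patients enrolled.

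**The concern.** The article identifies variables that drive infarct size, declines to stratify on them, and then does not commit to using them in the analysis. Three things are at stake.

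1. **Precision.** A *t* test leaves the variation due to location and delay in the error term. A short covariate list removes it without recruiting anyone.
2. **Choice of analysis.** An unadjusted test and an unranked regression sit side by side. Unless one is named as primary, the more favourable result could be put forward.
3. **Content of the model.** An instruction to adjust for every confounder does not confine the model to pre-treatment variables. Under Interventions, the infusion starts about 30 minutes before angioplasty. Under Primary and secondary outcomes, biomarkers are drawn immediately after reperfusion, at 6 to 8 hours and before discharge. Treatment could affect these, and adjusting for them could remove part of the effect being estimated.

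**Working it through.** **1. The plan's own figure.** Sample size uses n = 2(z_α + z_β)²S²/(MA − MB)² with 5% significance, 80% power, 10% loss and "a relative improvement up to 25% infarct size". It defines S in words only ("S is the variance of CMR determination for assessment for IS") and gives no number for S, MA or MB. The 66 per arm therefore cannot be reproduced, and I solved it backwards, taking a two-sided test (the article does not say):

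- Evaluable per arm: 66 × 0.90 = 59.4.
- (1.960 + 0.842)² ≈ 7.85.
- Standardised effect d = √(2 × 7.85 / 59.4) = 0.514. If loss was added as n × 1.10, then n = 60 and d = 0.511.
- Implied SD as a fraction of the control mean: 0.25 / 0.514 = 0.49, which is plausible but cannot be verified.

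**2. Power with and without covariates.** I took N = 120 (60 per arm) and d = 0.514. With p covariates explaining a share R² of the variance, the non-centrality is

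λ = d / √[(1 − R²)(2/60)(N − 3)/(N − 3 − p)], with N − 2 − p degrees of freedom.

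The factor (N − 3)/(N − 3 − p) charges for estimating the covariates. All R² values are assumptions.

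| Analysis | R² | λ | Power |
|---|---|---|---|
| Unadjusted | – | 2.816 | 0.80 |
| 3 covariates | 0 | 2.780 | 0.79 |
| 3 covariates | 0.1 | 2.930 | 0.83 |
| 3 covariates | 0.2 | 3.108 | 0.87 |
| 3 covariates | 0.3 | 3.322 | 0.91 |
| 30 covariates | 0.2 | 2.715 | 0.77 |

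With d = 0.511 the unadjusted power is 0.79. Before the small charge for covariates, efficiency 1/(1 − R²) is 1.11 at R² = 0.1 and 1.43 at R² = 0.3, equivalent to 11–43% more patients. Three useless covariates cost about one point of power.

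**3. Centre alone.** Simulation of two equal centres, blocks of six, 60 per arm, d = 0.514, 6,000 runs per setting:

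| Variance due to centre (assumed) | Type I error, t test | Type I error, with centre | Power, t test | Power, with centre |
|---|---|---|---|---|
| 2% | 0.046 | 0.049 | 0.80 | 0.80 |
| 5% | 0.042 | 0.047 | 0.81 | 0.82 |
| 10% | 0.041 | 0.052 | 0.80 | 0.83 |
| 20% | 0.027 | 0.047 | 0.81 | 0.88 |

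Omitting centre makes the test conservative. It adds no false positives, and the power lost is small unless the centres differ strongly.

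**4. Choosing between analyses.** Simulation under no treatment effect, three covariates, 8,000 runs. The figure is the chance that the best available p-value falls below 0.05:

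| Analyses to choose from | R² = 0.2 | R² = 0.4 |
|---|---|---|
| t test only | 0.049 | 0.052 |
| t test or 3-covariate regression | 0.074 | 0.082 |
| Rank test also available | 0.083 | 0.092 |
| Every covariate subset also available | 0.10 | 0.13 |

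**5. Chance imbalance.** With 60 per arm and an assumed 40–50% anterior infarcts, the exact binomial probability that the arms differ by 10 percentage points or more is 0.305–0.315.

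**The case against.** The case for leaving the plan alone has real force.

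- **The unadjusted test is valid and is what the trial was sized for.** This stands. Randomisation covers chance imbalance, so the 31% figure shows that imbalance is common and does not show that the test is wrong. Preferring a regression is an argument about efficiency, and its size depends wholly on an assumed R².
- **There is an implied order.** The listed tests are stated as firm intentions and the regression only as a possibility. That is a fair reading, but no test is tied to infarct size by name, so the ranking remains an inference.
- **A statistical analysis plan may settle this.** It may. The objection here is to what the article states: that the model is undecided, and that the candidate would take in every confounder.

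A reader might also draw stronger conclusions that the article does not support:

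- *The model will be chosen after the data are seen.* No time for the choice is given, and participants, care providers, investigators and image readers are blinded.
- *Post-angioplasty TIMI flow is a harmful covariate.* Table 2 excludes grades 0 to 2 and Primary and secondary outcomes requires grade 3, so as written it is constant.
- *There are too many covariates for about 120 patients.* No number is stated. In the calculation above, 30 covariates at R² = 0.2 took power below the unadjusted level, while three did not.
- *Ignoring centre biases the result.* It makes the test slightly conservative.

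**Conclusion.** The point holds as a free improvement and does not invalidate the planned test. Only unadjusted tests are firmly listed, centre is unused despite blocking within it, and the one adjusted model has neither a closed covariate list nor a rank.

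On precision, the loss is roughly 3 to 11 points of power if entry covariates explain 10–30% of variance. This assumes a two-sided test and the effect implied by 66 per arm. Most of the gain would come from location and delay, and little from centre. On selection, the 7–8% type I error applies only if the better of two analyses is actually reported. The article permits this by leaving the rank open, but does not say it will happen. The sponsor should make the change.

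**What to change.** Before unblinding, state the following in the protocol or analysis plan.

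1. The primary analysis is a linear regression of infarct size on arm, centre, infarct location (anterior or other, from the entry ECG or pre-angioplasty angiogram) and time from symptom onset to randomisation. The last of these is the pre-treatment part of time to reperfusion.
2. The unadjusted test is a sensitivity analysis.
3. The covariate list is closed and limited to pre-treatment variables. Biomarkers drawn at or after reperfusion are excluded.
4. The handling of clearly non-normal residuals is also set in advance, so that a rank test does not become a further option.

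The cost is a few sentences and three degrees of freedom out of about 120. Location is already recorded, onset time is needed for eligibility, and centre and randomisation time are known from allocation. No extra patients or visits are needed.
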